### Trial intervention

Using an approach informed by experience-based co-design [37], the STABILISE therapy programme was developed and refined through a series of workshops and other communications with patients and supporters, as well as input from therapists familiar with the component therapies.

Established psychological therapies for people with BD, such as CBT and group psychoeducation, include multiple skills to support people in managing symptoms and relapse, and some of these skills are applied to subsyndromal symptoms. STABILISE draws upon many of these skills. As with standard CBT, STABILISE includes a behavioural approach that seeks to promote re-engagement with valued activities and meaningful routine. Specifically, STABILISE recognises that instability in behaviours and affect in IEBS are related, and aims to help participants find a balanced, sustainable pattern of activity that enables them to live well within their situation, to support them to change their situation where possible and needed, and to make changes to patterns of behaviour that lead to problems or distress. This typically entails reducing mood-driven behaviour and increasing behaviours guided by the person’s values, plans or goals. These principles apply equally to depressed versus hypomanic states.

Standard techniques for bipolar symptom management tend to be based on the assumption that mood fluctuations build up over days and weeks, culminating in a relatively stable major episode. Consequently, these techniques may not be optimal for managing more rapid changes in affect. STABILISE draws upon techniques from DBT and emotion regulation therapies for affect management, and incorporates these within its behavioural framework. Recognising that people with bipolar disorder, particularly those with IEBS, have often experienced many years of threatening, uncontrollable shifts in affect, energy and motivation, STABILISE draws upon several key principles of DBT including an emphasis on validation of emotional experiences and a dialectical stance, balancing acceptance and change. For a summary of similarities and differences between STABILISE and established, related approaches please see Additional File 2.

The intervention consists of up to 20 individual therapy sessions (plus up to 2 initial assessment sessions) of behavioural therapy, delivered up to 7 months (30 weeks). Therapy ends after 20 sessions or 7 months, whichever is sooner, and participants can choose to space sessions out over more than a week if they wish or to take a short break from therapy. Sessions are an hour long as default but with the option for participants to agree shorter or longer (up to 75 min) session duration if needed. This is followed by a period of consolidation whereby participants can opt to see the therapist up to 3 times up until 12 months after starting therapy. All sessions will be audio-recorded (where participants consent to this) to allow for supervision and the refinement of a therapy adherence and competence measure.

Therapy will be delivered by at least three therapists with an existing training in cognitive behavioural, behavioural or dialectical behavioural therapy and experience of working with people with mood disorders. Therapists new to delivering the intervention will receive a 3-day training programme and all therapists will receive supervision every 1–2 weeks from the therapy developer or a STABILISE senior therapist whilst delivering therapy.

Therapy will be delivered face-to-face, online or by phone according to participant preference and what is feasible; local NHS service protocols will be followed in terms of telephone and online platform use. Face-to-face therapy will by default be delivered in the treatment centre; however, in keeping with the ethos of the approach (patient-centred, flexible, contextual and experiential) therapy sessions may take place outside of the centre if the participant wishes and it is appropriate and safe to do so. This may include practising activities together (e.g. visiting a shop) or sessions within the person’s home. Participants will complete the Beck Depression Inventory (BDI) [38] and Altman Self-Rating Mania Scale (ASRM) [39] prior to each session and the scores used to inform their care, as well as forming part of the research data collected.

It is anticipated that changes to the therapy protocol during the feasibility trial will be minor (i.e. will concern including or excluding specific techniques, or the wording and presentation of therapy materials, rather than the underpinning principles, therapeutic approach and overall structure). Changes to the therapy protocol will be timestamped allowing identification of which participants received which version.

The comparison arm in this trial is TAU. This was chosen because of the absence of a ‘gold standard’ therapy for inter-episode symptoms against which the novel therapy can be benchmarked. To characterise the content of TAU across trial sites, we will collect data on health services used by participants. There will be no restriction on the content of TAU; this includes no restrictions on participants accessing psychological therapies for bipolar disorder once entered into the study.

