**Methods:**

Patients will be randomised 1:1 to either Treatment as Usual (control arm) or Treatment as Usual plus STABILISE intervention (intervention arm). Follow up points will be at 14, 30 and 52 weeks post eligibility confirmation, with 30 weeks as the primary end point. We aim to recruit 60 individuals meeting diagnostic criteria for a Bipolar Spectrum Disorder, and reporting ongoing bipolar symptoms (low mood or mood instability) outside of a manic or severe depressive episode. Feasibility and acceptability will be examined through recruitment and retention rates, completion rates for the candidate primary outcome measures (PHQ9, ALS-SF, QoL.BD and BRQ) and feedback from participants on their experience of study participation and therapy. Proceeding to a definitive trial will be indicated if the following criteria are met: (i) trial participation is deemed, or can be made, sufficiently safe; (ii) recruitment rate indicates that larger-scale recruitment would be feasible (recruitment rate of at least two participants per month within at least one site, with mitigation plan if overall target sample size not met); (iii) for candidate primary outcome measure follow up data is available at 30 weeks from at least 75% of participants, or from between 55 and 74% with clear plan for improvement.

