Overall safety of intervention and trial procedures as determined by TSC and sponsor^a^	Cannot be made sufficiently safe for use in a definitive trial		Can be made sufficiently safe following modification		Sufficiently safe for use in a definitive trial	
Mean recruitment rate per site over 15 months	< 2 participants per month at both sites		< 2 participants per month at one site and target sample size not reached, with clear plan for improvement		≥ 2 participants at both sites OR < 2 participants at one site but overall target sample size reached^b^	
Outcome measure completion at 30-week follow-up point (completion of candidate primary outcome measure at primary end point)	< 55% of participants		Between ≥ 55 and < 75% of participants, with clear plan for improvement		≥ 75% of participants	
Level of completion of intervention (defined as attending at least 6 therapy sessions)^c^	< 50% of participants		50–89% of participants, with clear plan for improvement		≥ 90% of participants	

Red: Do not progress to the main trial (unless TSC agree exceptional circumstances and a mitigation plan is present); Amber: Progress if action plan to mitigate problems can be determined and agreed with the Trial Steering Committee (TSC); Green: Progress directly to the main trial

^a^Subsequent to reviewing information on adverse and serious adverse events arising during the trial

^b^To allow for a situation in which recruitment systems require a lead-in period at a site before becoming optimized, and this optimization period can then be accounted for in planning for a definitive trial

^c^Information will be collected on reasons for discontinuation to inform plan for enhancing retention in intervention and/or refinement of the estimand for a definitive trial [28]

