#### Additional measures

At the 30-week follow-up point, participants will complete a feedback questionnaire within which they will be asked to rate (on a scale from 1 to 4) their satisfaction with the therapy, how acceptable it was and the likelihood they would recommend it to a friend (for those in the intervention arm), and their overall satisfaction with the research element of the therapy (both arms), and also to give written comment on their answers to each questions and any general comments on the therapy or research. A brief feedback questionnaire will be sent to those exiting the study early, at the point they exit, if they have indicated they would be willing to complete this.

To monitor and evaluate intervention and study safety, an ‘Asking about adverse events’ form will be completed following the intake assessment (a researcher will check on participants’ wellbeing within a week of the intake assessment), and at the 14-, 30- and 52-week follow-up points. Members of the research team will also follow up with participants in relation to any potential adverse events mentioned in ad-hoc communications, therapy contacts or via HEQ completion.

Participants will be invited to rank outcome measures according to which they would most wish to experience change upon. Rankings will be conducted at baseline, and at the 30-week follow-up point.

Participants will be asked about their concordance with their prescribed psychiatric medication using the single, overall compliance question from the Brief Adherence Rating Scale (BARS [47]) at intake, 14 and 30 weeks.

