### Procedure

Informed consent will be taken prior to or at commencement of the eligibility assessment by a member of the study team; consent will be re-affirmed verbally prior to qualitative interviews. Following the initial eligibility assessment and completion of baseline measures, participants will be randomised to either STABILISE plus TAU, or TAU. Those allocated to the intervention arm will commence treatment approximately 2 weeks after being deemed eligible. Assessments at 14, 30 and 52 weeks will involve participants completing self-report measures either online or on paper, according to their preference, as well as speaking to a member of the research team (online, by telephone or in person) to complete the measures that require contemporaneous researcher involvement. A default procedure will be followed in cases where participants do not respond to requests to complete measures, with the procedure being tailored in accordance with individual patient preferences, as discussed following acceptance to the study. Figure 1 displays the measures completed at each time point.

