### Adverse events

We will monitor and record both serious and non-serious adverse events. Adverse event reports will be solicited at follow-up points and monitored during all research contacts and through inspection of HEQ responses. An adverse event (AE) is defined by the HRA as any untoward occurrence or worsening of an unintended sign, symptoms or disease that occurs during participation, regardless of any relation to participation. In the STABILISE study, an adverse event will be recorded only when medical/clinical assessment or treatment is sought for a new or worsening sign, symptom or disease, unless the event appears to be a result of participation in the study. An adverse event will be classified as serious if it results in death, life threatening injury or condition, permanent impairment to a body structure, body function or the capacity of the individual to function in daily life, hospitalisation or extension of existing hospitalisation, foetal death or a congenital abnormality or birth defect.

Symptoms of bipolar disorder themselves are not defined as adverse events. However, deterioration in mental state that results in the person accessing emergency support will be classed as an adverse event.

Any AEs that researchers or therapists believe may be study related, may merit a classification of ‘severe’ (even if not technically meeting SAE criteria) or may constitute an SAE will be required to be reported to the site PI, Trial Manager and the CI within 24 h. Other AEs must be reported to the PI, Trial Manager and CI within 1 week. The reporting period for all events and reactions will be from intake assessment to completion of the 52 week follow-up point.

The only expected reactions to the therapy and/or trial procedures are distress or symptom exacerbation (including behaviours such as self-harm, suicidal behaviour or substance use which may be considered to be part of the symptom set that individual typically experiences or may be considered to be coping responses in the face of distress or symptom exacerbation).

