It is recognised that those participants in the intervention arm have more contact with the study team (and therefore more opportunity to report adverse events) than do those in the usual care arm, by virtue of attending therapy sessions. Thus, we may expect a higher rate of adverse events reported in the former arm. In this study particular attention will be paid to those events that appear to be caused by research or therapy participation.

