### Criteria for discontinuation

Individual participants will discontinue their involvement if either (i) the participant does not wish to continue with the intervention and study; (ii) the participant experiences an unexpected serious adverse reaction (mental or physical health event that results in significant impairment, hospitalisation or death) that is judged to be the direct result of the intervention or trial participation, where discontinuation is judged to be in the best interests of the participant by the participant or sponsor (with advice from the Trial Steering Committee); (iii) the participant and/or therapy/research team believe that the intervention or trial participation will result in, or is likely to result in, a serious adverse reaction if continued; or (iv) the participant does not attend more than three consecutive therapy sessions without explanation; this will be judged to indicate discontinuation of therapy. Over the period that the participant does not attend sessions, efforts will be made by the therapist to contact the participant. Participant choice to discontinue therapy will not be assumed to mean automatic withdrawal from the trial.

Should an unexpected serious adverse reaction occur to either the therapy or the trial procedures, and this is judged to be directly related to trial participation or to the therapy, the trial will be temporarily halted pending investigation and analysis of the extent to which future risk can be mitigated against. If it is judged that this is not possible, the trial will be discontinued. This process will be led by the sponsor in collaboration with the TSC chair and CI. Should information come to light from external sources that indicate that the therapy intervention or trial procedures are unsafe, the same process will be followed.

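### Consolidation sessions may run to about week 54 from eligibility, but the stated adverse event reporting period closes at the 52-week follow-up

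*Protocol article*

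**What the plan says.** Under Trial intervention, the core course ends after 20 sessions or 30 weeks, whichever is sooner. A consolidation period follows, in which "participants can opt to see the therapist up to 3 times up until 12 months after starting therapy". That clock starts with therapy. The Procedure section sets the lag: "Those allocated to the intervention arm will commence treatment approximately 2 weeks after being deemed eligible".

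Follow-up runs on another clock. The abstract states: "Follow up points will be at 14, 30 and 52 weeks post eligibility confirmation". The Design section counts the same points from study entry.

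The Adverse events section sets a definite end: "The reporting period for all events and reactions will be from intake assessment to completion of the 52 week follow-up point". The last scheduled adverse event form falls at the same time, since after the check following intake it is completed "and at the 14-, 30- and 52-week follow-up points". The SAE analysis under Statistical analyses also covers 52 weeks.

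**The concern.** The end of permitted therapy and the end of adverse event reporting should coincide, or reporting should end later. Here they are counted from different starting points, and the therapy window closes last. In roughly weeks 52 to 54 the trial may still be delivering its experimental therapy to a participant whose reporting period, as written, has closed.

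This touches what the protocol says it cares about. It states that "particular attention will be paid to those events that appear to be caused by research or therapy participation". The safety progression criterion in Table 1 is judged by the Trial Steering Committee and sponsor "Subsequent to reviewing information on adverse and serious adverse events arising during the trial". A late reaction in an early participant could also matter to others: someone eligible on 1 April 2024 would reach week 54 on 14 April 2025, while recruitment is open until June 2025.

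**Working it through.** The plan gives no figure for this gap, so there is none to reproduce. The check is timeline arithmetic.

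**Inputs from the protocol article**
- Lag from eligibility to start of therapy: about 2 weeks (Procedure).
- Last consolidation contact: 12 months after starting therapy, at most 3 contacts (Trial intervention).
- End of adverse event reporting: completion of the 52-week follow-up (Adverse events), nominally week 52 from eligibility.
- Core therapy: up to 2 assessment and 20 therapy sessions, within 30 weeks (Trial intervention).

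**Length of the gap**

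Gap = lag + 12 months − 52 weeks.
- 12 months read as 52 weeks: 2 + 52 − 52 = 2.0 weeks.
- 12 months read as 365.25/7 = 52.2 weeks: 2 + 52.2 − 52 = 2.2 weeks.

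The last permitted contact is therefore at week 54.0 to 54.2.

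**Sensitivity (assumed departures, 12 months = 52 weeks)**

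| Start lag | 52-week assessment | Gap |
|---|---|---|
| 1 week | on time | 1 week |
| 2 weeks | on time | 2 weeks |
| 2 weeks | 1 week late | 1 week |
| 2 weeks | 2 or more weeks late | none |
| 3 weeks | on time | 3 weeks |
| 4 weeks | on time | 4 weeks |

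**Share of the consolidation window**

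The earliest end of core therapy considered is 22 weekly contacts starting at week 2: 2 + 21 = week 23. The latest is the full 30 weeks from week 2: week 32. The window to week 54 is then 31 or 22 weeks.
- 2/31 = 6.5%
- 2/22 = 9.1%

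**Participants who might have a contact in the gap**

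Assume 30 participants in the intervention arm (half of 60) and contacts timed independently and at random over the window.
- One contact each: 30 × 0.0645 = 1.9 to 30 × 0.0909 = 2.7.
- Three contacts each: 1 − (1 − 0.0645)³ = 18.1%, or 5.4 of 30; 1 − (1 − 0.0909)³ = 24.9%, or 7.5 of 30.
- No late contacts: zero.

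**Calendar**

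For a last participant eligible on 30 June 2025, week 52 is 29 June 2026 and week 54 is 13 July 2026. If the 28-month study period (Trial Status) runs from the start date of 28 March 2024, it ends on 28 July 2026.

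**The case against.** The strongest reply is that late sessions are not unobserved. The section on anticipated risks says that therapists and supervision watch for reactions, and that standard operating procedures on monitoring and reporting adverse events are followed. Those procedures are not shown. The halt rule begins "Should an unexpected serious adverse reaction occur to either the therapy or the trial procedures" and sets no cut-off at week 52. Additional measures has the team follow up possible events mentioned in therapy contacts, again with no end date. All of this stands. A reader might infer that nobody watches for harm in weeks 52 to 54, or that the halt rule lapses then. The documents support neither inference.

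A second reply is that the timings are loose. The lag is approximate, 12 months may simply be a rounding of the 52-week horizon, and reporting ends when the assessment is completed, not on a fixed date. This stands in part: a late assessment shortens or closes the gap. But a delay that happens by chance is not a safeguard, and a later start of therapy widens the gap.

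A third reply is that nothing in the results moves. This is right. The SAE risk difference and odds ratio cover the same 52 weeks in both arms, and the safety criterion is a judgement, not a count. A reader might infer that the between-arm safety comparison or a progression threshold is compromised, but neither depends on these two weeks.

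The remaining point is narrow. The Adverse events section gives one explicit end date for all events and reactions, and nothing in the article extends it to the last therapy contact.

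**Conclusion.** The mismatch is real and minor. As written, up to about 2 weeks of permitted therapy in the intervention arm falls outside the stated reporting period, given a 2-week lag and a 52-week assessment completed on time. What needs correcting is that period's end date; oversight as such continues.

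The length of the gap follows from the protocol's own statements. The number of people concerned does not. The estimates of about 2 to 3 of 30 with one contact each, and about 5 to 7.5 of 30 with three, rest on assumed random timing and on every participant using the optional sessions. They say nothing about how many events would be missed.

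**What to change.** Either of two small changes would do.

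1. In the intervention arm, continue adverse event reporting to the later of the 52-week follow-up and the last consolidation contact. List events after the 52-week follow-up separately. Keep the between-arm SAE risk difference and odds ratio at 52 weeks, so that both arms are compared over the same period. The cost is one changed sentence and about 2 more weeks of reporting for the few participants with late contacts. On the dates above this fits within the 28 months, with about 2 weeks to spare.
2. End consolidation contacts at the 52-week follow-up. The cost is about 2 weeks off a consolidation window of 22 to 31 weeks. No change to reporting is needed.

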### Outcomes and measures

As this is a feasibility trial, the primary outcomes relate to the key feasibility objectives. Additional File 3 details how each feasibility objective will be assessed.

#### Demographic information

At the baseline eligibility assessment, demographic information (age, gender, ethnicity, perceived financial status, sexual orientation) will be collected.

#### Patient-reported clinical outcome measures

In addition to the PHQ-9 and ALS, the following clinical outcome measures will be completed at baseline, 14, 30 and 52 week follow-up (see Additional File 2 for measure details): Bech Rafaelsen Mania Scale (BRMS [40], Brief Quality of life in Bipolar Disorder scale (QoLBD [41], Generalised Anxiety Disorder Questionnaire (GAD-7 [42]), Bipolar Recovery Questionnaire (BRQ [43]), Life chart self-report (a self-report of number and duration of depressive and manic episodes in the period since last assessment, completed at 14, 30 and 52 week follow-up points only, with the support of the researcher; Health Economics Questionnaire (HEQ [44]), EQ-5D-5L (health related quality of life). At this stage, candidate future primary outcome measures include the PHQ-9, ALS, QoL.BD and BRQ.

